### Study outcome

The primary outcome of interest is high (≥80%) and effective (patients receiving the full course of pneumonia treatment) coverage among under-five children (**Table 3**). The secondary outcome of interests are: treatment failure rate among young infants 7–59 days old with fast breathing and children 2–59 months old with chest indrawing and/or fast breathing pneumonia who received treatment from CCs; availability of essential commodities and supplies for managing childhood pneumonia; CHCPs’ knowledge of managing childhood pneumonia; caregiver’s knowledge and care-seeking practices regarding childhood pneumonia; and prevalence of pneumonia among under-five children, utilisation of CCs for pneumonia related symptoms; and treatment compliance.

**Table 3 T3:** Study enrolment and outcome assessment strategy

Activity	What	Who	When	Where	How
Case identification	Identify young infants with fast breathing pneumonia and children aged 2–59 months with fast breathing and/or chest indrawing pneumonia from data extracted from the service registers	Trained data extractors appointed by the study team	Twice in a week	Health facilities (CCs and union-level health facilities)	Trained data collectors will extract data from the registers or case record forms in the health facilities. From there, they will identify young infants with fast breathing pneumonia and children aged 2–59 months with fast breathing and/or chest indrawing pneumonia. They will provide this information to study-appointed nurses/paramedics who will conduct enrolment of the participants.
Screening and Enrolment	Enrol eligible young infants and children aged 2–59 months based on inclusion and exclusion criteria	Study appointed nurses or paramedics	One to three days after facility visit	Phone	Nurses and paramedics will screen the children based on the inclusion and exclusion criteria from the information received from study-appointed data extractors. They will contact the caregivers of the eligible children over the phone and take verbal consent for the home visit. They will enrol the children if consent is given by the caregivers.
Treatment provision and treatment documentation	A tool to document treatment provided to young infants with fast breathing pneumonia and children aged 2–59 months with fast breathing and/or chest indrawing pneumonia	Trained data extractors appointed by the study team	Twice in a week	Health facilities (CCs and union-level health facilities)	Trained data collectors will extract data on treatment provided by the health workers from the registers or case record forms in the health facilities
Treatment follow-up and outcome assessment	A tool to assess adherence to treatment given to enrolled young infants and children aged 2–59 months	Study-appointed nurses or paramedics	Day 7 and 14 of enrolment (visiting health facilities- CCs and union-level facilities)	Home	Trained nurses/paramedics will conduct home visits on days 7 and 14 of enrolment. They will interview caregivers to explore adherence to the treatment given to enrolled young infants and children aged 2–59 months. They will also assess the treatment given to enrolled young infants and children aged 2–59 months to explore treatment failure rate.

CC – community clinics

Treatment failure will be defined as: death anytime within 14 days of initial assessment; persistence of the fast breathing in young infants 7–59 days or persistence of chest indrawing and/or fast breathing in children 2–59 months old on day 7 of enrolment; any indication of hospitalisation (that is, with any sign of clinical deterioration) on day 7; and development of serious adverse event of the treatment (anaphylactic reaction, severe diarrhoea, disseminated and severe rash).

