In Bangladesh, pneumonia accounted for around 24% of all under-five deaths in 2022, with a mortality rate of 7 per 1000 live births [6]. Despite a high coverage of *Haemophilus influenzae* type b and pneumococcal conjugate vaccines (98–99%), only 46% of children with suspected pneumonia are taken to an appropriate healthcare provider [7]. In 2022, the country’s median integrated Global Action Plan for Pneumonia and Diarrhoea score was 68% overall and 81% for pneumonia specifically, falling short of the global target of 84% [7]. The care-seeking behaviour of its population is influenced by factors such as caregivers' knowledge, parental joint decision-making, mistrust of the healthcare system, faith in traditional care, spiritual beliefs, distance to health facilities, shortage of qualified staff, and household wealth [8–10]. Many children with pneumonia symptoms are taken to private sector providers, with only a small percentage seeking care from public health facilities [6]. The gaps in achieving high coverage of core interventions and the reliance on inappropriate care-seeking practices highlight the need for improved community-level pneumonia management in Bangladesh.

Global recommendations for low-resource settings indicate the adoption of the Integrated Management of Childhood Illness (IMCI) strategy for outpatient management of common childhood illnesses, including pneumonia. Developed by the World Health Organization (WHO) and the United Nations Children’s Fund (UNICEF) in the mid-1990s, the IMCI strategy promotes accurate identification of childhood illnesses in outpatient settings, appropriate combined treatment of all major illnesses, strengthened counselling of caretakers, and provision of preventive services [11–13]. It also emphasises the need for speeding up the referral of severely ill children and improving the quality of care at the referral level [11,13–15]. In home settings, it promotes appropriate care-seeking behaviours, improved nutrition, preventive care, and correct implementation of prescribed care [11,13–15].

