## METHODS

The goal of this study is to achieve high and effective population coverage of pneumonia treatment in under-five children in Bangladesh and to develop a scalable implementation strategy for contextual adaptation to other low- and middle-income countries (LMICs).

Our primary objective is to increase access to pneumonia treatment in under-five children to achieve high (≥80%) and effective population-based coverage (*i.e.*, patients receiving the full course of pneumonia treatment) in the study area. We also set five secondary objectives:

to increase care-seeking practices from appropriate healthcare providers for general danger signs and pneumonia-related signs of under-five children;to determine the rate of clinical treatment failure of young infants 7–59 days old with fast breathing and children 2–59 months old with fast breathing and/or chest indrawing pneumonia who received treatment from CHCPs;to assess the compliance with pneumonia treatment among young infants 7–59 days old with fast breathing and children 2–59 months old with fast breathing and/or chest indrawing pneumonia who received treatment from CHCPs;to explore the knowledge, perceptions, and experiences of health facility staff, CHCPs, and beneficiaries on the implementation of pneumonia management;to improve the availability of essential commodities in the CCs to manage pneumonia in under-five children.

We will achieve these objectives through three activities: designing an implementation delivery package for introducing the EMPIC in Bangladesh (activity 1); employing a continuous learning process during the implementation period to understand the prerequisites for the scale-up of the package (activity 2); and assessing whether the implementation delivery package worked by documenting the implementation process, understanding and assessing care practices, and exploring the experiences of health managers, health service providers, and caregivers related to the implementation of the package (activity 3).

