This study might also have several limitations. First, the clinical diagnosis of pneumonia will not be confirmed through radiological or microbiological assessments due to the impracticality of conducting these evaluations in community settings. Second, fast breathing in young infants could be attributed to various conditions such as viral respiratory infections, high fever, bronchiolitis, or malaria, which are unlikely to respond to amoxicillin. At present, differentiating between viral, bacterial, or mixed causes of pneumonia at the time of initial assessment remains a challenge, particularly in community-based settings. Third, EMPIC’s participatory design, involving policymakers and health workers, may introduce selection bias or conflicts of interest. These risks will be mitigated through independent data collection, triangulation across multiple sources, standardised tools, and PDCA cycles, and the engagement of stakeholders, which will be essential for ownership and sustainability. Furthermore, the 18-month study period will limit the assessment of long-term changes in health-seeking behaviours, treatment coverage, and outcomes. However, this implementation research focuses on feasibility, fidelity, acceptability, and integration of EMPIC into routine health services, providing foundational insights for longer-term evaluation and scale-up. Moreover, while we aim to provide insights for adaptation in other low-resource settings by documenting key factors, such as workforce capacity, supply chains, and community acceptability, our findings will be context-specific to the selected *upazilas* in Bangladesh. Another limitation will be caregiver recall of antibiotic administration, which is subject to recall and social desirability bias. Caregivers will be asked to show the prescription and medicine bottles during follow-up visits on days 7 and 14 to confirm whether antibiotics were indeed prescribed to the children; however, this procedure will not be employed for assessing treatment compliance. As the follow-up visits will be conducted on days 7 and 14, we anticipate that it will minimise the recall bias, as the recall period is short. Finally, the evaluation framework will rely on routine register data, caregiver recall, and household surveys, which are vulnerable to reporting bias, recall bias, and data quality issues. To minimise these issues, we will triangulate information from multiple sources. Specifically, the CHCP registers will record detailed clinical and treatment data for all under-five children presenting to CCs. Study nurses will conduct structured household community follow-ups on days 7 and 14 to assess treatment adherence, antibiotic use, and clinical outcomes of the pneumonia children, cross-checking caregiver reports with register entries. Baseline and endline household surveys will capture caregiver knowledge, care-seeking practices, and treatment outcomes, while health facility assessments will monitor service readiness, equipment, and drug availability. Qualitative interviews with caregivers, CHCPs, and health managers will document implementation processes, challenges, and contextual factors. Standardised tools, rigorous data collector training, periodic audits, and PDCA cycles with twice-weekly site visits will promptly identify and resolve operational or data-quality issues. Together, these complementary monitoring and data collection strategies will provide high-quality data to guide EMPIC implementation and policy decisions, forming a structured process evaluation framework aligned with WHO implementation research outcomes, including fidelity, adoption, acceptability, appropriateness and coverage.

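### The treatment-failure definition has no component for another antibiotic obtained before day 7, so a child rescued as an outpatient and free of signs on day 7 counts as a success

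*Protocol article*

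**What the plan says.** Under Study outcome, after Table 3, the protocol article sets out treatment failure as a list of four components.

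1. Death: "Treatment failure will be defined as: death anytime within 14 days of initial assessment".
2. Persistent signs: fast breathing in young infants, or "persistence of chest indrawing and/or fast breathing in children 2–59 months old on day 7 of enrolment".
3. Hospitalisation: "any indication of hospitalisation (that is, with any sign of clinical deterioration) on day 7".
4. A serious adverse event of the treatment: anaphylaxis, severe diarrhoea, or severe disseminated rash.

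The matching secondary objective in Methods is "to determine the rate of clinical treatment failure of young infants 7–59 days old with fast breathing" and of older children with fast breathing and/or chest indrawing, where a CHCP gave the treatment. The Study outcome section describes the same group as children with "chest indrawing and/or fast breathing pneumonia who received treatment from CCs" (CCs are community clinics).

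Table 3 places enrolment by phone one to three days after the facility visit, and home assessments on days 7 and 14. Foreseeable strengths and limitations says the nurses visit "to assess treatment adherence, antibiotic use, and clinical outcomes of the pneumonia children". It adds that caregivers will be asked to show prescriptions and bottles, to confirm that antibiotics were prescribed. Data analysis bases compliance on caregiver recall of giving the antibiotics that the CC prescribed.

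**The concern.** The failure rate is the study's measure of how children fare after CHCP treatment under routine conditions. Suppose a child does not improve, is taken to another outpatient provider, receives a different or additional antibiotic, and breathes normally by the day-7 visit. CHCP-given amoxicillin alone did not resolve that illness to the caregiver's or the second provider's satisfaction, yet the written definition gives no reason to count a failure.

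The path is plausible in this setting. The introduction says "Many children with pneumonia symptoms are taken to private sector providers, with only a small percentage seeking care from public health facilities", and the package itself promotes prompt care-seeking. No study assessment of signs is planned between the CC visit and day 7, which is when a switch would happen.

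The error runs in one direction. Leaving out rescued children can only lower the counted rate, and a larger sample does not remove the effect. The findings are meant to inform scale-up, so an estimate that is too low would make the strategy look better than it is.

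**Working it through.** **Step 1: classify the child under the definition.** Take a child who receives another antibiotic as an outpatient between the CC visit and day 7, survives to day 14, has no fast breathing or chest indrawing on day 7, and has no listed adverse event.

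| Component | Met? |
|---|---|
| Death within 14 days | No |
| Persistent signs on day 7 | No, signs have cleared |
| Indication of hospitalisation on day 7 | No if judged on that day; possibly yes if it covers the whole period up to day 7 and the child had deteriorated |
| Listed serious adverse event | No |

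Read literally, the child is a non-failure. Under the wider reading of the third component, a child who worsened may be caught. A child switched because signs persisted without worsening would still not clearly be caught, because persistence is tied to day 7.

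**Step 2: look for another place that would catch it.** Compliance covers only antibiotics prescribed from the CC. Antibiotic use is assessed at follow-up, but no text links it to failure.

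**Step 3: reproduce the planning figures.** Inputs are from Sample size and sampling strategy, Community follow-up. The formula is n = 1.96² × p(1 − p) / d².

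- Young infants, p = 0.08, d = 0.04: 3.8416 × 0.0736 / 0.0016 = 176.7 (stated 176; × 1.05 = 184.8, stated enrolment 185).
- Children 2–59 months, p = 0.06, d = 0.03: 3.8416 × 0.0564 / 0.0009 = 240.7 (stated 238, close; × 1.05 = 249.9, stated enrolment 250).

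The figures reproduce closely enough. They serve here only as a scale for the bias.

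**Step 4: an assumed range for the bias.** Let s be the share of all followed-up children who received another antibiotic for persistence or worsening before day 7 and met none of the four components. The documents give no value for s. If every such child is a true failure, the rate including them is the counted rate plus s. This is an upper bound.

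| Assumed s | Infants: hidden of 176 | Infants: rate if 8% counted | Older: hidden of 238 | Older: rate if 6% counted |
|---|---|---|---|---|
| 1% | 1.8 | 9% | 2.4 | 7% |
| 3% | 5.3 | 11% | 7.1 | 9% |
| 5% | 8.8 | 13% | 11.9 | 11% |
| 10% | 17.6 | 18% | 23.8 | 16% |

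The shift equals the planned margin at s = 4% in infants (0.04 × 176 = 7.0 children per district) and at s = 3% in older children (0.03 × 238 = 7.1 children per district).

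**The case against.** **A clinical-status endpoint is a legitimate choice.** An implementation study may ask only whether the child is well on day 7, whatever care came between. The outcome is secondary and descriptive, and the article contradicts itself nowhere on this point. That stands as a matter of preference. It is met by reporting both versions, since the objective and outcome tie the rate to treatment received from CHCPs at CCs.

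**The third component may already catch deterioration before day 7.** This stands as an ambiguity. It narrows the gap for children who worsened but does not clearly close it for those switched because of persistence alone.

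**Stronger readings that the documents do not support.**

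- A reader might infer from the introduction that most children treated at a CC will go on to a private provider. The text says many, not most, and it describes where symptomatic children in general are taken. Nothing reports second-provider use after CC treatment, so the path is plausible and its frequency unknown.
- A reader might infer that the rate will be judged against the 5.4% and 4.3% of the earlier trial. Those figures only motivate the planning values of 8% and 6%. No comparison or threshold is stated, and the documents do not say whether that trial counted an antibiotic change as failure.
- A reader might take the rates in the table as corrected estimates. They are assumed upper bounds. The article itself notes that fast breathing in young infants can have causes unlikely to respond to amoxicillin, so some switched children might have recovered anyway.
- A reader might assume that the data needed are already collected. Prescriptions and bottles are viewed to confirm prescribing. The article does not say that the source, date or reason for other antibiotics is recorded.

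**Conclusion.** The point holds as a gap in the outcome definition. The four-part list omits a substitute or additional antibiotic obtained elsewhere before day 7, and nothing else in the article supplies it. A child rescued as an outpatient and clear of signs on day 7 is scored a success, unless deterioration at any time up to day 7 is meant to count, which the text does not settle.

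The bias in the descriptive failure rate is downward and its size is unknown. Only under the assumption that every switched child is a true failure does a share of 4% (infants) or 3% (older children) match the planned margin of error. That is about seven children per district in each group, so a modest amount of switching could matter. The change is worth making because it is cheap and the error runs one way. The point concerns outcome classification only and proposes no treatment rule.

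**What to change.** Make three changes to the outcome definition and its reporting.

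1. Add a failure component: *receipt, before the day-7 visit, of a substitute or additional antibiotic not dispensed at the index CC visit, given for persistence or worsening of the illness*.
2. State whether deterioration that occurs before day 7 and has resolved by the visit counts under the hospitalisation component.
3. Report the failure rate under the current definition alongside the extended one, so that the contribution of antibiotic switches is visible.

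**Cost.** The change needs a short amendment to the definition. If the follow-up form does not already have it, it also needs an item on the source, date and reason for any other antibiotic, asked at home visits already planned. The reported failure rate will be somewhat higher. Some switches will reflect caregiver preference, and the stated reason rests on caregiver report. Restricting the component to persistence or worsening and showing both rates limits that problem without removing it.

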**Methods:**

This study will adopt an implementation research approach that integrates quantitative and qualitative methods. A delivery package will be co-developed with stakeholders to introduce enhanced pneumonia management through government systems in three phases within community clinics of selected *upazilas* in Kushtia and Dinajpur districts. We will use the plan-do-check-act cycle framework to evaluate implementation, track progress, identify gaps, and test potential solutions. Data collection methods will include health facility assessments, data extractions from routine registers and monthly reports, household surveys, and community follow-ups of under-five children with pneumonia on days 7 and 14 post-treatment. The primary outcome is high (*i.e.* ≥80%) and effective coverage (*i.e.* patients receiving the full course of pneumonia treatment) of pneumonia treatment in under-five children. Secondary outcomes include treatment failure rates among under-five children with pneumonia; availability of commodities and supplies for pneumonia management; health worker knowledge, caregiver awareness and care-seeking practices regarding childhood pneumonia; pneumonia prevalence among under-five children; community clinic utilisation for pneumonia-related symptoms by under-five children; and treatment compliance.

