**Figure 3 F3:**
[figure not shown]
Theory of Change underpinning EMPIC intervention. CC - community clinic, CHCP – community healthcare provider, EMPIC - Enhanced Management of Pneumonia in Community, IMCI – Integrated Management of Childhood Illness, MoHFW – Ministry of Health and Family Welfare, PDCA – Plan-Do-Check-Act.

#### Activity 3

Health facility assessments will be conducted at baseline and end-line to evaluate the service availability and readiness of CCs, using structured tools to assess equipment, drugs, and logistics for pneumonia management, as well as CHCPs’ knowledge regarding management of childhood pneumonia. We will extract data from routine registers to evaluate recording and reporting practices, and will monitor monthly utilisation reports through central management information systems. Community follow-up of the pneumonia-classified children on the 7th and 14th days of CC visit will involve household visits by study-nurses to assess treatment failure rates and adherence to guidelines. Baseline and endline household surveys will measure caregivers' knowledge, care-seeking practices, and treatment outcomes, defining treatment failure based on specific clinical criteria.

We will explore the experiences of health managers, CHCPs, and caregivers through in-depth and key informant interviews which will focus on contextual factors, including social determinants of health, cultural beliefs, caregiver practices, and CHCPs and health system constraints (such as workload assessment) that influence care-seeking and treatment adherence. Insights from these interviews will inform iterative refinement of the intervention and interpretation of fidelity, acceptability, and adoption outcomes. This comprehensive data collection (**Table 1**) will inform continuous improvements in pneumonia management at CCs.

**Table 1 T1:** Data collection procedure throughout the study period

	Baseline	Q1	Q2	Q3	Q4	Q5	Q6	Endline
Health facility assessment	X	O	O	O	X	O	O	X
Knowledge assessment of service providers	X	O	O	O	O	O	O	X
Household survey	X	O	O	O	O	O	O	X
Data extraction	O	X	X	X	X	X	X	O
Community follow-up	O	X	X	X	X	X	X	O
Qualitative exploration	X	X	X	X	X	X	X	X

X – active data collection period for the specified activity, O – no data collection (activity not conducted during that time period

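### The treatment-failure outcome has no single day 0, and as worded it can miss non-fatal deterioration outside day 7

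*Protocol article*

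**What the plan says.** The follow-up days have three starting points.

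- Abstract, Methods: follow-up is "on days 7 and 14 post-treatment".
- Activity 3: "Community follow-up of the pneumonia-classified children on the 7th and 14th days of CC visit".
- Table 3, follow-up row: "Trained nurses/paramedics will conduct home visits on days 7 and 14 of enrolment". The timing cell of the same row reads "Day 7 and 14 of enrolment (visiting health facilities- CCs and union-level facilities" and the parenthesis closes there.

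The screening and enrolment row of Table 3 places enrolment at a phone call, timed "One to three days after facility visit". The condition is consent: "They will enrol the children if consent is given by the caregivers". Cases are found by reading the registers twice a week (Table 3; Other data collection methods).

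The failure definition below Table 3 has four components.

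- Death: "death anytime within 14 days of initial assessment".
- Persistence of signs: on day 7 of enrolment.
- Hospitalisation or deterioration: "any indication of hospitalisation (that is, with any sign of clinical deterioration) on day 7", with no start named.
- Serious adverse event of treatment: no window given.

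The objective and the outcome both refer to children who received treatment from community healthcare providers or CCs. The 5% loss allowance in the sample-size section is applied to enrolled children.

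**The concern.** A failure rate needs one time zero, a window for each component, and a stated population. Here the components of one composite run on different clocks, and the clock for the home visits is itself described in different ways. Two field teams could each follow the article and score the same child differently.

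The deterioration component is also narrower than the follow-up that the study pays for. A nurse visits on day 14 and death counts up to day 14, but a non-fatal deterioration between the two visits has no place in the definition.

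Finally, a child enters the analysis only after a caregiver has been reached by phone and has agreed. The article does not say what happens to a child who dies or is admitted before that call. The results are meant to inform scale-up of home treatment, so readers will take this rate as the clinical safety signal.

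**Working it through.** **1. The plan's own figures.** The follow-up is sized with n = z²p(1−p)/d², z = 1.96.

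- 7–59 days: p = 0.08, d = 0.04. 3.8415 × 0.0736 / 0.0016 = 176.7, against 176 stated. 176 × 1.05 = 184.8, against 185 enrolled.
- 2–59 months: p = 0.06, d = 0.03. 3.8415 × 0.0564 / 0.0009 = 240.7, against 238 stated. 238 × 1.05 = 249.9, against 250 enrolled.

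These agree closely enough. The problem lies in the definition, and no sample size changes.

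**2. The clock.** If enrolment is the phone consent, k = 1 to 3 days after the visit:

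- day 7 of enrolment = day 7 + k = day 8 to 10 after the visit;
- day 14 of enrolment = day 14 + k = day 15 to 17 after the visit.

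If enrolment means the facility visit, k = 0 and the visits fall on days 7 and 14.

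**3. Twice-weekly extraction.** Two extractions per week leave two gaps that add to seven days, so in whole days the longer gap is at least four. A child seen just after the extraction that opens that gap is first found about four days later, beyond the one-to-three-day enrolment window. This affects only some children.

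**4. Hypothetical children against the definition** (days counted from the CC visit; all survive except the fourth).

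| Course | Scored as |
|---|---|
| Admitted day 3, home and well by day 7 | Literal reading: not a failure. If day 7 means reported at that visit: failure |
| Well on day 7, admitted day 11, visit clock | Not a failure on either reading |
| Signs present on day 7, gone by day 9 | Failure on the visit clock; not a failure if enrolled on day 2 and seen on day 9 |
| Died day 11 | Failure |
| Well on day 7, deteriorating on day 9 | Not a failure on the visit clock; failure if enrolled on day 2 and seen on day 9 |

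The first two rows show that the restricted window only removes failures. The third and fifth show that a later clock can remove or add them, so its net direction is unknown.

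**5. What a missed share would mean (assumption only).** If a share f of all failures falls outside the counted window, the observed rate is p(1−f). The article gives no value for f.

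| f assumed | True 8% observed as | True 6% observed as |
|---|---|---|
| 10% | 7.2% | 5.4% |
| 25% | 6.0% | 4.5% |
| 50% | 4.0% | 3.0% |

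Each planned margin is half the planning rate (4 of 8, 3 of 6), so the shortfall equals the margin only if half of all failures are missed. This is a scale for judging the issue, not an estimate.

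**The case against.** The strongest counter-reading is the parenthesis in the follow-up row of Table 3. It may gloss enrolment as the facility visit, which would agree with Activity 3 and leave one clock. The abstract's wording would then be loose summary. This is plausible and means that the shift of one to three days is not certain. But the enrolment row of the same table puts enrolment at the later phone consent, so the conflict within Table 3 remains.

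Second, the day-7 wording may mean as established at the day-7 visit, including earlier admissions. That would rescue the child admitted on day 3. It does not rescue non-fatal deterioration after the day-7 visit.

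Third, a reader might infer that children who die or are admitted before the call are excluded. The article does not say so. A caregiver can still be reached and consent, and the death component starts at initial assessment, before any call. The inclusion and exclusion criteria are mentioned but not listed, and a full protocol may deal with this. What stands is an open risk of selective loss.

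Fourth, the outcome is secondary and descriptive, with no comparator and no decision threshold. That limits the weight of the point but does not remove it, because this is the rate that the follow-up is sized to estimate.

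**Conclusion.** The point holds as a defect of definition. The stated time anchors conflict, by one to three days if enrolment is the phone call. The deterioration component omits non-fatal events on days 8 to 14 as worded and, on a literal reading, admissions resolved before day 7. That omission can only lower the count; how far cannot be derived from the document.

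Three stronger conclusions are tempting and are not supported. A reader might infer that every one of these features lowers the reported rate; the late clock has no known net direction, and early losses are a risk rather than a rule. A reader might infer a specific undercount by letting the 6% planning rate decay over the extra days; that 6% is for the whole composite, not for persistent signs alone, and the article gives no resolution rate. A reader might also infer that the result cannot be compared with the 5.4% and 4.3% cited from the earlier trial; its failure definitions are not shown, so this cannot be judged.

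**What to change.** 1. Reconcile the abstract, Activity 3, Table 3 and the failure definition to one time zero. The CC visit is the natural choice: Activity 3 already uses it and it is consistent with the death component. Schedule both home visits from it.
2. Give every component a window from that time zero, including serious adverse events. Define the hospitalisation or deterioration component as any occurrence from time zero to the day-14 visit, asked at both existing visits. Report the day-7-only version as a sensitivity analysis.
3. Record vital and admission status at the enrolment call, and count known early deaths and admissions as failures.
4. Report the number of treated register cases not enrolled, with reasons. Do not treat unknown outcomes as non-failures. Status at the call cannot supply outcomes for families who are unreachable or refuse, so these cases should be shown separately and not absorbed into the denominator.

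The cost is protocol wording, slightly more form work at the call and at the two visits, and a possibly higher reported failure rate. No extra visits are needed and the sample sizes do not change. The change concerns outcome measurement only and proposes no rule of clinical management.
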